### Blinding

Nurses who administer the interventions and assess the outcomes might be aware of group allocation due to their participation in the training to manage the SCION-PAIN program. Patients are not informed about group assignment, but might be aware of it due to unmasking information from nurses. Therefore group allocation perception of included patients will be assessed at the end of trial 28th day after discharge.

### Implementation

Adult cancer patients with persistent pain will be recruited by the nurses of the participating wards under the guidance of a research nurse. Participants will be included in the trial if they meet inclusion criteria and have signed informed consent (see Figure 2). To ensure the implementation of the intervention, quality audits will be conducted in the intervention groups in both study centers based on the guidelines of the Royal Collage of Nursing [20] and the German Network of Quality Assurance in Nursing Care. The audit will be based on (1) regular monitoring of the trained nurses' knowledge about the training module, and (2) on an additional comparison of nursing records with study documentation for 10% of all included patients.

**Figure 2 F2:**
[figure not shown]
Trial profile

### Statistical methods

The statistical analysis of the primary outcome patient related barriers to pain management will be conducted based on hierarchical models for the analysis of cluster randomized trials [19], including a random intercept for the respective ward. Due to our limited number of wards we a priori specified to statistically adjust the analysis by covariates (age, sex, diagnose, metastasis, performance status (ECOG), pain management/CPMI [21], pain duration, cancer treatment [22-24], depression and anxiety [7] that are significantly (P < 0.1) different at baseline. We plan to test baseline differences not routinely but because we expect significant baseline differences due to experience of previous CRT in a similar setting with 16 clusters where we found systematic and explainable differences between groups at baseline [25]. Baseline differences will be judged by simple t- and χ^2^-tests.

Subgroup analyses will be undertaken by checking interaction between well established covariates (anxiety, depression and pain intensity [7]) and primary outcome. An intention to treat approach will be used for the analysis. The trial will be reported according to the guidelines of the consolidated standards of reporting trials (CONSORT) extension for cluster randomized controlled trials [26].

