### Outcomes

The effectiveness of SCION-PAIN program will be assessed by the following outcome measures at the individual patient level:

Primary outcome is the difference in patient related barriers to management of cancer pain (Barriers Questionnaire II) between control and intervention group [13].

The secondary outcome measures include:

1. intensity of pain (sensory dimension)

2. impact of pain and interference of pain in the patient's life (reactive dimension) [15]

3. Coping with pain [16]

4. Adherence to pain medication [17] and

5. HRQoL [18]

The outcome measures above will be assessed at trial inclusion, at discharge and 7, 14 and 28 days after discharge. The effectiveness of SCION-PAIN program will be assessed on an individual patient level by comparing the patient related barriers at day 7 after discharge in control versus intervention group.

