### Sample size

Sample size was calculated based on the t-test (α = 0.05) for cluster randomized controlled studies [19] with an assumed clinically relevant difference of 0.4 points (SD 0,7) per BQ II item, an intra cluster correlation (ICC) of 0.05 and a power of 80%. These assumptions yield a sample size of 208 study participants. To allow some moderate drop out, 240 participants will be included into the study.

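### The primary model's pre-specified covariate list omits baseline BQ-II, so the day-7 comparison gives up precision and would not be adjusted even if the arms differed at inclusion

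*Protocol article*

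**What the plan says.** Under Outcomes, the article names BQ-II as the primary outcome and gives the measurement schedule: "The outcome measures above will be assessed at trial inclusion, at discharge and 7, 14 and 28 days after discharge". A pre-intervention value is therefore planned, because under Interventions the first session follows inclusion. The same Outcomes section defines the primary contrast as the day-7 level in control versus intervention, not a change score.

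Under Statistical methods, the primary model is hierarchical with a random intercept for ward. Adjustment is described as specified a priori and limited to "covariates (age, sex, diagnose, metastasis, performance status (ECOG), pain management/CPMI [21], pain duration, cancer treatment [22-24], depression and anxiety [7", each entering only if the arms differ on it at P < 0.1 by a simple t- or chi-squared test. The section adds that significant baseline differences are expected, on the experience of an earlier 16-cluster trial in a similar setting. Nowhere does the article place baseline BQ-II in the model.

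The design inputs are under Sample size. The target effect is "an assumed clinically relevant difference of 0.4 points (SD 0,7) per BQ II item". The ICC is taken as 0.05, the target power is 80%, and the resulting total is 208 patients.

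**The concern.** The baseline value of the outcome is the natural first covariate in an analysis of a later level of the same outcome. Here it is due to be collected anyway. The article sets up an adjustment scheme because it expects imbalance, yet the scheme cannot respond to imbalance in the endpoint itself. Arms that differed clearly on BQ-II at inclusion would still be compared on unadjusted day-7 scores, unless a correlated listed variable such as anxiety or depression happened to pass the P < 0.1 screen and carried part of the difference.

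Two things are at stake: the precision of the primary estimate, and how a positive or null result can be read if the arms visibly started at different levels of barriers.

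**Working it through.** **Inputs.** From Sample size: difference 0.4, SD 0.7, ICC 0.05, α = 0.05 (two-sided assumed; the article does not say), 208 patients before the dropout allowance. From Methods and Randomization: 18 wards in matched pairs, taken as 9 per arm. Assumed: baseline to day-7 correlation r = 0.5, range 0.3 to 0.7; equal ward sizes; the same SD and ICC at baseline as at day 7.

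**The plan's own figure.** Ignoring clustering, the total is 2 × 2 × [0.7 × (1.960 + 0.842)/0.4]² ≈ 96. With m = 208/18 = 11.56 patients per ward, the design effect is 1 + 10.56 × 0.05 = 1.528, and 96.1 × 1.528 ≈ 147. A cluster-level t-test with 16 df gives 149; with 8 df, for nine matched pairs, it gives 184. So 208 is not reproduced, but it errs on the safe side. The present point does not depend on it.

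**Unadjusted precision.** Variance of a ward mean in SD² units: 0.05 + 0.95/11.56 = 0.05 + 0.0822 = 0.1322. SE of the arm difference: 0.7 × √(2/9 × 0.1322) = 0.120 points. Noncentrality: 0.4/0.120 = 3.33. Power: 87.9% with 16 df, 83.1% with 8 df.

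**Adjusted precision.** Two versions bracket the answer. If baseline explains only within-ward variance, the ward-mean variance becomes 0.05 + (1 − r²) × 0.0822. If it explains variance equally at both levels, it becomes (1 − r²) × 0.1322.

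| r | Variance reduction (within only / both) | SE, points (within only / both) | Power, 16 df (within only / both) |
|---|---|---|---|
| none | – | 0.120 | 87.9% |
| 0.3 | 5.6% / 9% | 0.117 / 0.114 | 89.6% / 90.6% |
| 0.5 | 15.5% / 25% | 0.110 / 0.104 | 92.5% / 95.1% |
| 0.7 | 30.5% / 49% | 0.100 / 0.086 | 96.3% / 99.2% |

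**Effect of a realised baseline difference.** A difference of 0.2 SD is 0.2 × 0.7 = 0.14 points. With the same slope within and between wards, it carries r × 0.14 into the unadjusted day-7 contrast: 0.07 points at r = 0.5 (0.07/0.4 = 17.5% of the target), 0.042 at r = 0.3 (10.5%) and 0.098 at r = 0.7 (24.5%).

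The SE of a chance baseline difference is √(2/9 × 0.1322) = 0.171 SD, so 0.2 SD is 0.2/0.171 = 1.17 SE. The two-sided probability of exceeding it is 0.24 (normal) to 0.26 (t, 16 df), or about 1 in 8 in the direction favouring the intervention. This ignores any gain from pair matching.

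**The case against.** **The list may not be exhaustive.** The article condenses a fuller plan, and no sentence excludes a baseline outcome term. It is true that nothing excludes it expressly. But the article does not leave adjustment for later: it gives a named list and an entry rule and calls them a priori. Followed as written, baseline BQ-II stays out, and a later plan that added it would change the stated rule.

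**The unadjusted analysis is valid and not short of power.** This stands. Planned power was 80%, and the stated inputs give about 88% at 208 (83% with 8 df). The gain from adjustment rests on r, which the article does not give; at r = 0.3 it is modest.

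**Chance imbalance is not bias.** This also stands. Over repeated randomisations the unadjusted contrast is unbiased for chance imbalance, and its SE of 0.120 already contains that variability. The 0.07-point shift and the SE reduction are therefore largely the same gain seen two ways and must not be added together.

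**A reader might infer that recruitment is unconcealed and the result therefore biased.** The documents do not establish this. Randomization states that allocation is concealed at cluster and individual level. There is reason for caution: wards are randomised before the study, ward nurses recruit (Implementation), and nurses who deliver the intervention may know the allocation (Blinding). Selective recruitment is thus possible, but not shown.

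**A reader might also count the absence of baseline pain intensity as an inconsistency.** It is not one. Pain intensity is named only for "checking interaction between well established covariates (anxiety, depression and pain intensity [7]) and primary outcome", which is a subgroup question, and the article gives no figure showing that omitting it as an adjustment variable costs anything.

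**Conclusion.** The point holds as a missed improvement in the primary analysis, not as an invalid or underpowered one. The stated rule leaves the endpoint's own baseline out of the model even if the arms differ on it, in a trial of 18 wards whose authors anticipate baseline differences.

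The size depends on an assumed correlation and on how far baseline BQ-II explains between-ward as well as within-ward variance. The SE and power figures also assume equal ward sizes, no gain from matching and, for power, 16 df. If r were near zero the precision loss would be negligible.

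A baseline difference produces true bias only if it arises from selective recruitment; otherwise it is a conditional shift already allowed for in the SE. The schedule provides for a baseline BQ-II in each patient, but how complete it will be is not stated.

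**What to change.** In Statistical methods, state that the primary hierarchical model regresses day-7 BQ-II on arm, with individual baseline BQ-II as a fixed covariate and the ward random intercept, and that the baseline term is included whatever any baseline test shows. Add a simple pre-specified rule for missing baseline values, so that no patient is lost from the intention-to-treat analysis for want of one. Adding baseline pain intensity is optional.

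The cost is a sentence or two of text and one regression coefficient. BQ-II at inclusion is already scheduled, so there is no extra patient burden and no change to the sample size.

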## Methods

In two German university hospitals, eighteen inpatient wards with each at least 10% of patients diagnosed with cancer will be randomized. Patients will be included if they are aged 18 to 80 years, have a cancer diagnosis, an average pain intensity score of ≥ 3.0 (on a 0 to 10 NRS), pain persistence for more than 3 days, the ability to read, write, and understand German, a scheduled follow up appointment at the clinic, and signed written informed consent.

Patients will be excluded if they have a limited performance status (ECOG 4), documented ongoing alcohol or drug abuse, surgery within the last 3 days or showing disorientation regarding date, place and situation.

The study will be performed according to the ICH-GCP principles and was approved by the regional ethics committees of Martin-Luther-University Halle-Wittenberg and Technical University Munich.

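### The primary model's covariates are chosen by P < 0.1 baseline tests that ignore ward clustering; a fixed prognostic set would be better calibrated and usually more powerful

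*Protocol article*

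**What the plan says.** The Statistical methods section of the protocol article specifies a hierarchical model with a random ward intercept for the primary outcome. It names ten candidate covariates: age, sex, diagnosis, metastasis, ECOG, the pain management index, pain duration, cancer treatment, depression and anxiety. Only those "that are significantly (P < 0.1) different at baseline" enter the model. On the screening tests it says: "Baseline differences will be judged by simple t- and" χ²-tests. No ward term is mentioned for these tests, and no covariate is named as always included.

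The section calls this adjustment specified in advance. It justifies testing by an earlier cluster trial with 16 clusters, in which the arms differed at baseline.

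Elsewhere, Methods says that "eighteen inpatient wards with each at least 10% of patients diagnosed with cancer will be randomized", Sample size assumes an outcome ICC of 0.05, and Randomization says that wards are matched in pairs on clinical profile.

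**The concern.** There are two separate faults.

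- **The screening test does not fit the design.** Patients on one ward resemble each other, so a test that treats about 240 patients as independent understates the variance of the difference between arms. It flags chance differences more often than its nominal 10%.
- **The criterion is the wrong one.** A baseline P value measures how far the arms differ, not how strongly the covariate predicts BQ II. A strong predictor at P = 0.15 stays out, and an irrelevant variable at P = 0.05 goes in.

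Fixing the list and threshold therefore does not fix the model. At stake are the calibration of the primary P value and confidence interval, and the precision that planned adjustment for prognostic covariates would give.

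**Working it through.** **Inputs from the protocol article.** Difference 0.4 and SD 0.7 per BQ II item (0.4/0.7 = 0.57 SD), α = 0.05 (two-sided assumed), power 80%, outcome ICC 0.05, 208 patients before and 240 after the drop-out allowance, 18 wards. This gives 240/18 = 13.3 patients per ward, or 208/18 = 11.6. Covariate ICCs and the share of outcome variance explained (R²) are not given and are assumed below.

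**1. The plan's own figure.** Per arm without clustering: 2 × (1.960 + 0.842)² × (0.7/0.4)² = 48.07. The design effect is 1 + 12.33 × 0.05 = 1.617, so the total is 2 × 48.07 × 1.617 = 155.4. Adding two wards per arm as a small-cluster correction for matching gives 155.4 + 4 × 13.33 = 208.8, close to the stated 208. That correction is inferred, and the point does not rest on it. With 208 patients on 18 wards and a t reference on 16 df, power without any adjustment is 87.9%.

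**2. Flag rate of the screening test.** For a covariate that differs only by chance, ignoring matching, the rate is 2 × [1 − Φ(1.645/√DE)], with DE = 1 + 12.33 × ICC.

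| Covariate ICC | DE | 1.645/√DE | Flag rate |
|---|---|---|---|
| 0.05 | 1.617 | 1.294 | 19.6% |
| 0.10 | 2.233 | 1.101 | 27.1% |
| 0.30 | 4.700 | 0.759 | 44.8% |

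At ICC 0.05, about 10 × 0.196 = 2.0 covariates enter by chance. At least one enters in 1 − (1 − 0.196)¹⁰ = 89% of trials if the covariates are independent.

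**3. Effect on the primary test, ten covariates.** Simulation with 18 wards of 12, outcome ICC 0.05, SD 0.7 and a REML random-intercept model. Each result is based on 4,000 to 9,000 runs. Covariate ICC is 0.05, except 0.10 in the R² = 10% row. Fixed means that all ten are always entered.

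| R² | Type I, rule (t, 16 df) | Type I, fixed (t, 16 df) | Type I, rule (Wald z) | Power at 0.4, rule (t) | Power at 0.4, fixed (t) |
|---|---|---|---|---|---|
| 0 | 4.6% | 4.7% | 6.1% | 88.4% | 87.5% |
| 10% | 4.2% | 4.5% | 5.8% | 89.4% | 91.1% |
| 20% | 3.7% | 4.7% | 5.1% | 90.8% | 93.6% |
| 40% | 2.9% | 4.7% | 4.0% | 93.0% | 98.1% |

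At R² = 40% under the rule, the mean standard error is 0.115 but the true SD of the estimate is 0.105. The model goes unadjusted mainly when imbalance is small. The estimate then varies less than its standard error says, and the test becomes conservative.

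At a smaller difference of 0.3 points, power is 66.7% under the rule against 73.3% fixed at R² = 20%, and 70.5% against 85.6% at R² = 40%.

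**4. Effect with five covariates.** Same wards, t on 16 df, five uncorrelated covariates.

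- Each at r = 0.25 (R² = 5 × 0.0625 = 31%): type I error 2.0-3.0% under the rule against 4.0-4.4% fixed; power at 0.57 SD 86-92% against 96%, a gap of about 4 to 10 points.
- Each at r = 0.15 (R² = 5 × 0.0225 = 11%): type I error 3.4% and 4.5% in two runs, against 4.3% and 4.7% fixed; power about 90% against 92-92.5%.

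**The case against.** The strongest defence is that the rule is mechanical. List, threshold and tests are all fixed, so the analyst has no free choice. A reader might infer from the many possible covariate combinations that the sponsor could pick a favourable model; the text does not allow that. What remains is that the data choose the model.

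A reader might also infer that diagnosis and cancer treatment will be flagged almost regardless, because wards specialise. The Randomization section speaks against this, since wards are matched on clinical profile. Take wards of 12, covariate ICC 0.20 and, as an assumption, pairs that share 80% of the ward variance. The variance factor falls from 0.8 + 12 × 0.20 = 3.2 to 0.8 + 12 × 0.04 = 1.28, and the flag rate from about 36% to about 15%. The rates in the table are therefore upper figures for variables that the matching captures.

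Real imbalance is also plausible. Wards are allocated before patients are recruited, and ward nurses who may know the allocation recruit them. The flag rates and simulations assume chance imbalance only. This objection stands, but it argues for adjusting on a set fixed beforehand, not for letting an invalid test decide.

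Finally, power under the rule stays above 80% at the planned effect in every scenario. With prognostic covariates it is slightly higher than with no adjustment (90.8% against 89.1% at R² = 20%). Both facts stand.

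**Conclusion.** The concern holds as a matter of calibration and efficiency. It should be fixed, but it does not invalidate the trial.

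- The screening test runs at about twice its stated level at a covariate ICC of 0.05, before any effect of matching, and it selects on the wrong criterion.
- With covariates that explain about 20-40% of outcome variance and a t reference, the primary test runs at about 2-4% instead of 5%.
- Against fixed adjustment for prognostic covariates, about 2 to 10 percentage points of power are lost at the planned effect.

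These sizes depend on assumed R² values, covariate ICCs and the reference distribution. With weak covariates the type I effect is small. With a Wald z reference it is partly or fully offset by the usual inflation with few clusters.

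Two stronger readings are not supported. A reader might infer that the rule raises the false-positive risk, but in these simulations it never does so materially relative to the fixed model, and with prognostic covariates it lowers it. A reader might infer that the trial becomes underpowered, but the loss exists only relative to fixed adjustment.

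**What to change.** Delete the P < 0.1 rule and the baseline significance tests. Name a short fixed set of prognostic covariates before outcome data are analysed: baseline BQ II, which the Outcomes section already schedules at inclusion but which is not among the ten candidates, plus a few listed ones such as depression, anxiety, ECOG and pain duration. Enter them in the random-intercept model whatever their observed imbalance, show the baseline table without P values, and report the unadjusted model as a sensitivity analysis.

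The cost is about one sentence of text and a few patient-level degrees of freedom; no new data are needed. The set should stay short: when none of the ten covariates predicts the outcome, entering them all costs about one point of power (87.5% against 88.4% under the rule).

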### Time plan

The SCION-PAIN program is a further development of a previous self care program for management of chemotherapy induced anorexia, nausea and emesis published elsewhere [25]. The development of the special pain program began in February 2007 and was finished in June 2008. The patient recruitment started in October 2008 and will continue until December 2009. The trial will be completed in July 2010.

## Discussion

We expect SCION-PAIN program to be effective in improving patients' self management abilities of cancer pain.

Methodical strength of our study is the random group allocation minimizing known and unknown potential sources of bias.

It is hypothesized that patients who receive the multi modular structured intervention will have less patient related barriers to the management of cancer pain. Our hypothesis is based on Greens PRECEDE Model explaining health behavior [27,28]. The model was specified for pain related behavior within the conceptual framework by Yates et al. [29]. There are three categories influencing pain related health behavior identified by the model. Those are: (1) *predisposing factors*, such as beliefs, attitudes and perceptions; (2) *enabling factors*, as knowledge and skills and (3) *reinforcing factors*, i.e. feedback by family or health professionals.

The SCION-PAIN program focuses on predisposing and enabling factors because patient related barriers, such as misconceptions about opioid use, crucially interfere in establishing and maintaining a proper pain related self management [7].

As Figure 3 shows in variation to Green and Yates the factors we newly organized according to patients' resources for pain related self management. Therefore the SCION-PAIN program distinguishes between patients' resources regarding *knowledge, self care actions *(enabling factors) and *believes *(predisposing factors). According to this structure pain related self management will be best in patients which are *acting *(show high adherence to medication, communicate with health care professionals, and use complementary strategies) based on a sufficient body of *knowledge *and supportive positive *attitudes*.

**Figure 3 F3:**
[figure not shown]
**Conceptual framework based on PRECEDE Model **[27,28]** and Yates et al**.[29].

The purpose of our trial is to contribute evidence on interventions improving self management in cancer patients with pain. As the SCION-Pain program will be integrated in nurses' daily working schedule and applied through regular ward staff, thus will be tested under "real world" circumstances, the results may be generalized to similar settings. Therefore the SCION-Pain program suggests a practical and pragmatic approach that is focused on patients' resources.

## Abbreviations

CPMI: (Cleeland pain management index); HRQoL: (Health related quality of life); PMR: (Progressive Muscle Relaxation according to E. Jacobson); PRECEDE: (Predisposing, Reinforcing and Enabling factors, and Causes in Educational Diagnosis and Evaluation); SCION: (Self Care Improvement through Oncology Nursing); ECOG: (Eastern Cooperative Oncology Group).
